### Data management

The data collected from each patient will be recorded in a standardized case report form (CRF), and the CRF will be transmitted to the coordinating center (Affiliated Rehabilitation Hospital of Nanchang University) after the trial is completed. The researchers responsible for data management at the center will store these data anonymously on the Research Electronic Data Capture platform. Only researchers responsible for data management can access its content. After all data are stored, the database will be locked and sent to the research statistician for analysis according to the predetermined statistical analysis plan.

### Statistical analysis

Statistical analysis will be performed using R software. For demographic and baseline data, the quantitative data that conform to a normal distribution will be expressed as mean ± standard deviation (
$\bar{x}$
 ± *s*) and differences between groups will be analyzed using the independent samples *t*-test. The quantitative data that do not conform to a normal distribution will be expressed as median (interquartile range, IQR) and differences between groups will be analyzed using the Mann–Whitney U test. The qualitative data will be analyzed using the chi-square test or Fisher’s exact test. For the efficacy indicators, in order to detect changes in CRS-R, FOUR and GCS scores over time and differences between groups, a linear mixed-effects model (LMM) with repeated-measures analysis from the “nlme” package in R software will be used. *Post-hoc* exploratory subgroup analyses will explore the effects of taVNS on subgroups according to different levels of consciousness and different etiologies. For safety indicators, HRV and blood pressure data were tested for normal distribution and analyzed using the paired-samples *t*-test or Wilcoxon Signed-rank test. Differences between groups in the incidence of adverse events were analyzed using the chi-square test or Fisher’s exact test. *p* < 0.05 was considered statistically significant.

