**Methods:**

We aim to recruit 382 patients with prolonged DOC, and divide them into an active stimulation group and a sham stimulation group. The patients in the active stimulation group will receive bilateral synchronous taVNS with a 200 μs pulse width, 20 Hz frequency, and personal adjusted intensity. The sham stimulation group will wear the same stimulator but without current output. Both groups will receive treatment for 30 min per session, twice per day, 6 days per week lasting for 4 weeks. The clinical assessment including Coma Recovery Scale-Revised (CRS-R), Full Outline of Unresponsiveness (FOUR), Glasgow Coma Scale (GCS), and Extended Glasgow Outcome Scale (GOS-E) will be conducted to evaluate its efficacy. Heart rate variability (HRV), blood pressure, and adverse events will be recorded to evaluate its safety.

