**Figure 2 fig2:**
[figure not shown]
**(A)** Bilateral synchronous taVNS device; **(B)** stimulation sites and electrodes.

The device is presented with Mode A and Mode B. One is active stimulation, and the other is sham stimulation with no current output. Both modes exhibit identical screen displays and button operations (the current intensity can be adjusted, while other parameters are fixed to the values mentioned above). This makes researchers and device operators unaware of which stimulation is the active one. The two groups will receive treatment for 30 min per session, twice a day, 6 days a week for 4 weeks. The above treatment parameters and time refer to our previous single-center study (24) and peer studies (19, 23, 25). Bilateral synchronous taVNS will be performed at the same time before the start of the routine rehabilitation therapy in the morning and afternoon every day, under the operator’s continuous monitoring.

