**Figure 3 fig3:**
[figure not shown]
Evaluation process. CRS-R, Coma Recovery Scale-Revised; FOUR, Full Outline of Unresponsiveness; GCS, Glasgow Coma Scale; GOS-E, Extended Glasgow Outcome Scale.

The cardiovascular system is doubly innervated by the sympathetic and parasympathetic nerves. The vagus nerve is a mixed cranial nerve that contains parasympathetic nerve fibers. In theory, stimulating the vagus nerve may increase the risk of its mediated bradycardia and hypotension. Heart rate variability (HRV) analysis can provide information on the balance between the sympathetic and parasympathetic pathways (28). It is a useful tool for evaluating cardiac autonomic regulation (28). Therefore, we will use a heart rate chest strap (Maijin Intelligent Technology Co., Ltd., Qingdao, China) and the Elite HRV smartphone application (Elite HRV Inc., Asheville, NC, United States) to collect and analyze patients’ HRV information. Specifically, placing the sensor of the chest strap at the level of the heart in front of the chest. Adjusting the length of the elastic strap to ensure close contact between the electrode area and the skin. Connecting the chest strap to the Elite HRV application on the phone via Bluetooth. We will collect and analyze HRV information of the patients for 30 min before and during the first taVNS, including mean heart rate, mean RR, the standard deviation of normal-to-normal RR intervals (SDNN), the root mean square of successive differences (RMSSD), the proportion of NN50 divided by the total number of normal-to-normal RR intervals (PNN50), low-frequency (LF) power, high-frequency (HF) power, total power, and LF/HF ratio. The chest strap records the cardiac electrical activity and extracts heart rate data from the electrocardiogram (ECG) waveforms, which has detection results comparable to Holter ECG (29–31). For blood pressure, we will record it once separately before and during the patient’s first taVNS. In addition to our recordings, ECG monitoring will also be performed on patients during each stimulation to detect vital signs.

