In taVNS studies for other diseases, the current intensity was typically determined based on the patient’s perceptual threshold [e.g., 200% of the perceptual threshold (43)] or pain threshold [strongest painless stimulus (44)]. However, these methods are not applicable for patients with DOC due to their perception and communication deficits. NCS-R is a validated and highly sensitive tool for assessing the nociceptive pain responses of patients with DOC through motor, verbal and facial aspects (26). In this protocol, we use NCS-R to assess the tolerance of patients to taVNS. Specifically, the current intensity is gradually reduced in steps of 0.5 until the patients exhibit no pain response (NCS-R score < 4).

Although reports indicating that bilateral taVNS has little impact on parasympathetic nerves and is considered safe (36, 37), we will still evaluate its effects on heart rate and blood pressure. HRV serves as a crucial metric for assessing cardiac autonomic regulation by quantifying variations in sinus rhythm (28). Therefore, we will use HRV to measure the impact of taVNS on the sympathetic/parasympathetic balance. Typically, HRV is calculated using a Holter ECG, a process that can be quite intricate. Given that this is a multicenter study, the tools and methods for collecting and analyzing Holter ECG data vary significantly across sub-centers. Additionally, large-sample multicenter trials require procedures that are straightforward and easily executable. Hence, we opt for a solution involving a chest strap coupled with the EliteHRV software. This solution provides acceptable agreement compared to ECG (30, 31). In our protocol, this alternative ensures consistency, simplicity, and operability of multi-center trials.

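### Heart rate variability and blood pressure are tested only before versus during stimulation, with no between-arm contrast, so this part of the safety evaluation cannot attribute a change, or its absence, to taVNS

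*Protocol article*

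**What the plan says.** All references are to the protocol article.

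- **Role of the measures.** The abstract (Methods) lists them as safety evidence: "Heart rate variability (HRV), blood pressure, and adverse events will be recorded to evaluate its safety".
- **What is measured.** Data collection says "We will collect and analyze HRV information of the patients for 30 min before and during the first taVNS", and then lists nine indices. For blood pressure, "we will record it once separately before and during the patient"'s first session.
- **Test.** Statistical analysis says "HRV and blood pressure data were tested for normal distribution and analyzed using the paired-samples" t-test or the Wilcoxon signed-rank test. No between-group test is given for these measures.
- **Intended inference.** The Discussion says "we will use HRV to measure the impact of taVNS on the sympathetic/parasympathetic balance".
- **Available control.** The Intervention protocol describes two device modes that look the same to the operator: "One is active stimulation, and the other is sham stimulation with no current output".

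The same Statistical analysis section does name between-group analyses for baseline data, for the CRS-R, FOUR and GCS scores (linear mixed-effects model) and for adverse events (chi-square or Fisher's exact test).

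**The concern.** A paired test asks whether the average value moved between two periods. Here the periods differ in more than the current. The second always follows the first, the device has been fitted, pain is being scored with the NCS-R, and the patient has been at rest for longer. Any of these may move heart rate, HRV or blood pressure in both arms alike. The randomised sham mode can remove such shared movement, but only if active is compared with sham.

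The point matters because Data collection names bradycardia and hypotension as the theoretical risks of vagal stimulation, and the Discussion explains that the earlier single-centre trial used the left ear alone for safety reasons. Bilateral stimulation is therefore the step whose autonomic effect needs a controlled answer. With paired tests only, ordinary drift can look like a stimulation effect, and a real effect can be cancelled by drift the other way. If each arm is tested separately, one significant and one non-significant result may be taken for a difference between arms, which it is not.

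**Working it through.** **1. Number of patients.** The documents give no sample size for HRV or blood pressure, so the CRS-R figure is used. Inputs from Sample size: means 10.93 and 9.28, SDs 4.99 and 4.38, α = 0.05, power 90%, 10% loss.

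- Difference = 10.93 − 9.28 = 1.65. SD = √[(4.99² + 4.38²)/2] = 4.695.
- Two-sided, the normal formula gives 171 per arm. The t-based solution is 171.1, hence 172. One-sided would give 139, so the plan's 172 is two-sided.
- 344 / 0.90 = 382.2, in line with the stated 382.

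The plan's own figures reproduce and are not in dispute. The value n = 172 per arm is carried forward. As the measurements fall in the first session, before most losses, up to 382/2 = 191 per arm may have data.

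**2. Assumption.** Stimulation has no effect. Both arms share the same before/during shift s, in SDs of the individual change. The documents give no value, so s runs from 0.10 to 0.30.

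**3. Paired test in the active arm.** The statistic is non-central t with n − 1 = 171 degrees of freedom and non-centrality s√172 = 13.115s. The rejection probability is p = P(|T| > t₀.₉₇₅).

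**4. Separate tests in each arm.** The arms are independent, so they disagree with probability 2p(1 − p).

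**5. Between-arm test of the change.** The shared shift cancels. In 20,000 simulated trials per setting, rejection was 5.0%, 4.7% and 5.1% at s = 0.10, 0.20 and 0.30.

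| Shared shift s (SD of change) | 13.115s | Paired test significant, active arm | Arms disagree | Between-arm test |
|---|---|---|---|---|
| 0.10 | 1.31 | 26% | 38% | about 5% |
| 0.15 | 1.97 | 50% | 50% | about 5% |
| 0.20 | 2.62 | 74% | 38% | about 5% |
| 0.30 | 3.93 | 98% | 5% | about 5% |

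The 50% disagreement at s = 0.15 is the largest value that 2p(1 − p) can take, so the whole range should be read. With 191 per arm, the paired test is significant in 28%, 54%, 79% and 99% of trials. If the arms were pooled for the paired test (n = 344), which the text does not rule out, the first three figures become 46%, 79% and 96%, and the last is practically 100%.

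**6. Masking.** Suppose a true effect of −0.30 SD meets a shared shift of +0.30 SD. The mean change in the active arm is then zero and the paired test rejects in 5% of trials. A between-arm test has non-centrality 0.30 × √(172/2) = 2.78 and detects the effect with about 79% power.

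**7. Is the between-arm test adequate at this size?** At 172 per arm it has 80% power for a difference of 0.30 SD and 90% power for 0.35 SD.

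**The case against.** The best defence is that these are secondary safety measures and that safety does not rest on them alone. This stands. A reader might infer that the whole safety conclusion lacks a control, but adverse events are compared between arms, with cardiac arrest among the listed examples. The gap is confined to HRV and blood pressure.

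A reader might also infer that the sham arm is unused. The text does not show this. Data collection speaks of the patients without limiting them to one arm, so sham patients may be measured and paired-tested too. It does not say that both groups are measured either. In any case, a paired test within the sham arm does not estimate the active-minus-sham difference.

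Three further extensions do not hold:

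- **Regression to the mean in the single blood pressure reading.** This would need selection on an extreme pre-session value, and no entry criterion selects on that reading. Noise in one reading widens the SD but creates no drift.
- **Multiplicity over nine HRV indices.** The indices overlap (mean heart rate and mean RR; total power and its LF and HF components), and a between-arm analysis of all nine would carry the same multiplicity. It is a separate matter.
- **Measurement in the first session only, and no planned analysis of session-by-session monitoring.** This concerns data collection, not the choice of test. The plan says "ECG monitoring will also be performed on patients during each stimulation to detect vital signs", and adverse event recording is open-ended, so events seen on the monitor can enter the between-arm comparison. The limitations paragraph already acknowledges the single blood pressure readings.

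Finally, the analysis plan mentioned under Data management could add a between-arm comparison. That is possible, but the protocol is not silent here: it names a test, and the test does not answer the stated question.

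**Conclusion.** The point holds for HRV and blood pressure only. The named paired tests cannot separate stimulation from whatever else changes between the two periods, so they do not support the attribution to taVNS that the Discussion intends.

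Over the assumed shared shifts of 0.10 to 0.30 SD, the false-signal rate in the active arm is 26% to 98%, against about 5% for a between-arm test. These rates rest on the assumed shift, on independent arms with the same SD of change, and on 172 patients per arm. With no shift at all, the paired test keeps its 5% level. The defect in the inference does not depend on any particular value, because without the contrast the size of the shift is unknown.

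The plan does not say that a significant result in one arm and not in the other would be read as a difference; that is a risk of the chosen test. The primary outcome, the randomisation, the sample size and the adverse event comparison are untouched. This should be fixed, but it does not threaten the trial's main result.

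**What to change.** In Statistical analysis, replace the paired tests as the inferential analysis of HRV and blood pressure by a between-arm comparison of the value during the session, adjusted for the value before it. Use ANCOVA with centre and the VS/UWS or MCS stratum as covariates, on the log scale for LF, HF and total power. Report the active-minus-sham difference with its 95% CI (a ratio for the logged measures). Keep within-arm paired results as description only.

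In Data collection, state that HRV and blood pressure are recorded in both arms, at the first active or sham session.

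The cost is a change of wording, to be made before unblinding. No extra patients are needed. If sham patients are already measured, as the text permits, no new measurements are needed either. If they are not, each sham patient adds one HRV recording covering both periods and two blood pressure readings.

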The first clinical application of VNS was the treatment for intractable partial seizures (12). Its clinical application was approved by the Food and Drug Administration (FDA) in 1997 (13). Currently, besides intractable partial seizures, the FDA has approved VNS for medication-resistant depression (14), episodic cluster headaches (15) and moderate-to-severe upper extremity motor impairments following chronic ischemic stroke (16).

According to the International Consensus Based Review and Recommendations for Minimum Reporting Standards in Research on Transitional VNS (Version 2020) (17), there are four currently accepted VNS methods: cervically implanted VNS (iVNS), transcutaneous cervical VNS (tcVNS), transcutaneous auricular VNS (taVNS), and percutaneous auricular VNS (paVNS). Among them, taVNS is a safe, non-invasive, and easy-to-use treatment option, compared to iVNS (18). The first use of VNS for DOC was published in 2017 with a case report (19). A VS/UWS due to cardiac arrest developed to MCS after 4 weeks of taVNS. In the same year, another case report also reported that a patient with VS/MCS developed to MCS after 4 weeks of iVNS (20). Subsequently, 5 (21), 10 (22), and 14 (23) patients with DOC were treated with VNS in 3 case series (1 iVNS and 2 taVNS). These case series indicated that VNS improved the behavioral responses (conscious state) of patients and was safe and feasible for DOC.

However, these uncontrolled case reports (19, 20) and case series (21–23) only provided weak Class IV and Class V evidence of treatment efficacy. It cannot be ruled out that the impacts are from spontaneous recovery, especially considering the acute to subacute background of the enrolled patients. Recently, we provided the highest level of evidence for the efficacy and safety of VNS for DOC with a single-center double-blind randomized controlled trial (RCT) (28 active versus 29 sham stimulation) (24). It indicated that 4 weeks’ taVNS significantly improved the Coma Recovery Scale-Revised (CRS-R) score of MCS patients, and without significant side effects. In order to further confirm and validate the efficacy and safety of taVNS, as well as to provide more comprehensive and reliable evidence, we propose here a multicenter, double-blind, stratified, two-arm RCT.

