### Sample size

The required sample size was calculated based on the results of our previous single-center RCT (24). In which, the difference of total CRS-R score between the taVNS group and the sham stimulation group after treatment was 10.93 ± 4.99 vs. 9.28 ± 4.38. We set the test power (1-β) to be 90%, the type I error rate (α) to be 0.05, and the group allocation of the two groups to be equal. The calculated sample size was N1 = N2 = 172. Considering that 10% of patients will be lost during follow-up, a total of 382 patients with pDOC will eventually be enrolled.

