## Discussion

Despite great efforts in medication therapy, neuromodulation and physical rehabilitation, the successful treatment strategy of DOC remains limited, primarily due to a profound lack of comprehension of the underlying pathophysiology (32). In recent years, there has been a growing interest in VNS as a potential therapeutic approach, encompassing both invasive and non-invasive techniques. The invasive method involves surgically transmitting electrical pulses directly to the exposed cervical vagus nerve. Notably, the vagus nerve asymmetrically innervates the heart, and stimulating the right cervical vagus nerve can result in electrical signals being directly fed into the sinoatrial node, thereby heightening the risk of adverse cardiac events, such as arrhythmia. Conversely, stimulating the left vagus nerve poses a significantly lower risk of such complications. Thus the left vagus nerve is typically the preferred target for invasive method (33). However, this method is expensive and complex to operate. TaVNS, on the other hand, offers an economical, easier to implement and noninvasive alternative. It stimulates the auricular branch of the vagus nerve (ABVN) by targeting the skin of the outer ear, specifically the cymba conchae and cavum conchae (34).

Our previous study demonstrated the efficacy and safety of taVNS through the left ear. It provided the highest level of Class II evidence currently available (24). However, it was a single-center study with a limited sample size. Additionally, as a preliminary study, taVNS was solely administered through the left ear for safety considerations. Nevertheless, some literature indicated that non-invasive stimulation of the ABVN was not associated with adverse cardiac events. This is attributed to its selective stimulation of afferent fibers, which are processed by the brain before reaching the heart, rather than directly activating the heart’s pacemaking nodes (35). This effectively mitigates the side effects associated with efferent (visceral) fiber activation. Additionally, several studies have corroborated the security of bilateral taVNS (36, 37). Thereby, our current protocol aims to administer bilateral synchronized taVNS, aiming to boost treatment effectiveness, taking into account that brain damage can occur on the left, right, or both sides in DOC patients.

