This protocol still exists some limitations. Firstly, given the complexities of neuroimaging and electrophysiology in multicenter trials, our focus will primarily be on patients’ behavioral outcomes, while neglecting neuroimaging or electrophysiology programs. Secondly, due to the difficulties associated with continuously collecting blood pressure data, we will limit our collection to a single measurement before and during taVNS. This approach may somewhat diminish the statistical power compared to continuous blood pressure monitoring. Thirdly, the parameters utilized in this protocol are based on our previous single-center RCT and other relevant studies. There is currently no consensus on the optimal parameters for taVNS. Future studies should focus on determining the optimal parameters for specific patient populations, as well as investigating potential dose–response relationships and individual factors that may affect treatment outcomes.

In conclusion, the clinical treatment of DOC is challenging. TaVNS is an economical, non-invasive, promising, bottom-up neuromodulation. This protocol aims to provide multicenter, large-sample, and more effective Class II evidence for the efficacy and safety of taVNS for DOC. It will advance the field of treatment options for patients with DOC.

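### The only between-arm safety analysis is a p<0.05 test of adverse events with low power for small-to-moderate harm; the safety conclusion should rest on risk differences with confidence intervals

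*Protocol article*

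**What the plan says.** - **Aim.** The title names efficacy and safety together. The abstract's Discussion says the results will let the authors investigate both. The closing paragraph of the Discussion promises "more effective Class II evidence for the efficacy and safety of taVNS for DOC".
- **Between-arm safety analysis.** The Statistical analysis section states: "Differences between groups in the incidence of adverse events were analyzed using the chi-square test or Fisher’s exact test". The threshold is p "< 0.05 was considered statistically significant". No effect measure or interval is mentioned alongside the test.
- **Other safety measures.** "HRV and blood pressure data were tested for normal distribution and analyzed using the paired-samples" t-test or the Wilcoxon signed-rank test. These are before-versus-during comparisons and do not compare the arms.
- **Size.** The Sample size section works from the CRS-R difference in the group's earlier single-centre trial: "We set the test power (1-β) to be 90%, the type I error rate (α) to be 0.05". It then adds for loss: "Considering that 10% of patients will be lost during follow-up, a total of 382 patients with pDOC will eventually be enrolled". It gives no adverse-event rate and no safety margin.
- **Events.** Data collection lists skin burns at the stimulation sites, a set of systemic events described as mostly unrelated to the stimulation, and mortality.
- **The earlier trial.** The Introduction says of 28 active and 29 sham patients that treatment "significantly improved the Coma Recovery Scale-Revised (CRS-R) score of MCS patients, and without significant side effects". The Discussion later writes: "Our previous study demonstrated the efficacy and safety of taVNS through the left ear".

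**The concern.** A test of difference can reveal harm, but its failure to reach significance does not show that harm is absent. For uncommon events in a trial of this size, p>0.05 is the likely result even when a real excess exists. With the test as the only stated between-arm safety analysis, the trial could report no significant difference while its data remained compatible with a clinically relevant excess.

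This matters more here for two reasons. The Discussion says the earlier trial stimulated only the left ear out of caution, whereas this one stimulates both sides, so the earlier data do not settle the question. And skin burn is a device-related harm that the protocol itself anticipates. With no current output in the sham arm it should be close to absent there, and a sparse table of that kind is where Fisher's test is weakest.

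**Working it through.** **1. The plan's own figure.** Inputs from Sample size: means 10.93 and 9.28, SDs 4.99 and 4.38, power 90%, alpha 0.05 (taken as two-sided), allocation 1:1.

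- Difference = 10.93 − 9.28 = 1.65. Pooled SD = √[(4.99² + 4.38²)/2] = 4.695.
- n per arm = 2(1.960 + 1.282)² × 4.695² / 1.65² ≈ 170.1, so 171. The t-based version gives 172, as stated.
- 2 × 172 / 0.90 = 382.2, stated as 382, which is 191 per arm.

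The stated size reproduces. It is built on CRS-R and says nothing about safety.

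**2. Power of the adverse-event test.** The protocol gives no event rates, so all rates here are assumptions. Method: sum the binomial probabilities of all 2×2 tables in which the two-sided test gives p<0.05. The miss rate is one minus that sum.

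| Sham vs active | Fisher miss, 191 per arm | Uncorrected chi-square miss, 191 per arm | Fisher miss, 172 per arm |
|---|---|---|---|
| 0% vs 2% | 81% | 47% | 87% |
| 1% vs 3% | 84% | 73% | 87% |
| 2% vs 4% | 88% | 80% | 89% |
| 5% vs 10% | 61% | 53% | 66% |
| 10% vs 15% | 74% | 69% | 76% |
| 10% vs 20% | 25% | 21% | 30% |
| 5% vs 15% | 11% | 8% | 15% |
| 0% vs 5% | 8% | 1% | 14% |

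Power is low in the first five rows, moderate for 10% vs 20%, and good in the last two. For 80% power, 5% vs 10% would need 435 per arm and 2% vs 4% would need 1,141.

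**3. An event absent under sham, such as a burn.** With k events on active and none on sham, two-sided Fisher p = 2 × C(191,k)/C(382,k).

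- k = 5: 2 × (191·190·189·188·187)/(382·381·380·379·378) = 2 × 0.0304 = 0.061.
- k = 6: multiply by 186/377, giving p = 0.030. Six events to none is therefore the smallest significant split.

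Interval for 5/191 vs 0/191 (Newcombe, from Wilson limits):

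- Active: 2.62%, Wilson limits 1.12% to 5.98%. Sham: 0%, Wilson limits 0% to 1.97%.
- Lower limit = 2.62 − √[(2.62 − 1.12)² + 1.97²] ≈ 0.14 points.
- Upper limit = 2.62 + (5.98 − 2.62) = 5.98 points.

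The interval lies just above zero and reaches 6.0%, while Fisher's test calls the same data non-significant. The uncorrected chi-square would give z = 0.02618/√(0.01309 × 0.98691 × 2/191) = 2.25, p ≈ 0.024. But the expected count is 2.5 per arm, where Fisher's test is the conventional choice.

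**4. What the trial could say with intervals.** The approximate 95% half-width for a risk difference at 191 per arm is 1.96 × √[2p(1 − p)/191]: 2.8 points at an event rate of 2%, 4.4 at 5%, 6.0 at 10% and 9.2 at 30%. For no events among 191, the one-sided 95% upper bound is 1 − 0.05^(1/191) = 1.6%; the two-sided version is 1.9%.

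**The case against.** The strongest reply is that nothing in the protocol is wrong as written. Chi-square or Fisher comparison of adverse events is ordinary in a trial sized for efficacy, and being sized on CRS-R is no fault. Interval methods and rules for interpreting safety usually sit in the analysis plan. Data management refers to a predetermined plan that is not shown, so their absence from an article is no finding. Safety is also watched through HRV, blood pressure, ECG monitoring at every session, burn recording and mortality. All of this stands. The point is therefore limited to the stated test being too weak for the stated claim.

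Two stronger readings are tempting, and the documents support neither.

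- **A reader might infer that the trial will declare taVNS safe if p>0.05.** No section sets such a rule. The Introduction and Discussion sentences on the earlier trial make the reading plausible, but they concern that trial only. The Discussion adds that it was single-centre with limited numbers, and the word significant in the Introduction may have been meant clinically. The earlier event counts are not shown.
- **A reader might infer that the test would miss most relevant harms.** That depends on event rates and on a definition of relevant harm, and the protocol gives neither. Large excesses would be found with about 90% power at 191 per arm.

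It can also be said that reading the excluded excess from the interval sets no margin in advance. That is true. The proposal improves the estimate and the wording of the claim; it does not turn the trial into a formal safety test.

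**Conclusion.** The point holds as a worthwhile, inexpensive improvement, not as an error that invalidates the plan. Safety is a headline aim, and the one between-arm safety analysis stated is a significance test in a trial sized on CRS-R. Under the assumed rates, Fisher's test at 191 per arm misses small-to-moderate excesses 61% to 88% of the time (0% vs 2%, 1% vs 3%, 2% vs 4%, 5% vs 10%, 10% vs 15%). It misses 5% vs 15% or 0% vs 5% only 11% and 8% of the time. A non-significant result therefore cannot by itself support the promised evidence of safety.

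The size rests on three assumptions: the event rates, two-sided testing, and Fisher's test being used for sparse events. Uncorrected chi-square has more power, but the pattern is the same for 1% vs 3%, 2% vs 4%, 5% vs 10% and 10% vs 15%; for 0% vs 2% it still misses 47%.

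**What to change.** In Statistical analysis, and in the analysis plan, for skin burns, each listed adverse event, any adverse event and death:

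- Report the count and percentage per arm and the risk difference (active minus sham) with a 95% score-type confidence interval (Newcombe or Miettinen–Nurminen). Give an exact upper bound where a count is zero.
- State that the safety conclusion is drawn from the interval, in particular its upper limit, and that p>0.05 will not be taken as evidence of safety. The chi-square and Fisher p-values can stay as descriptive.
- Word the safety claim in the final report as the size of excess risk that the data exclude.

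This takes a few sentences and no extra patients, visits or data. The downside is a more modest claim: for an uncommon event the trial can exclude only an excess above a few percentage points.
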